### Outcomes

#### Overview

The primary outcome is a participant-defined goal, whose fulfillment is assessed at the end of the study using a Likert scale ranging from 1 (“far below expectations”) to 10 (“far above expectations”) [38].

Participants can choose their own goal from a range of options: increase fruit and vegetable consumption, increase physical activity, reduce alcohol consumption, stop smoking, improve sun protection behavior, and reduce the number of weekly hypoglycemic episodes (the latter only for T1D participants).

The secondary outcomes are: frequency of app use, time spent using the app, consistency in data recording, changes in eating habits, increase in physical activity, reduction in smoking and alcohol consumption, changes in sun protection behavior, total cholesterol, high-density lipoprotein (HDL) cholesterol, low-density lipoprotein cholesterol, non-HDL cholesterol, triglycerides, weight, BMI, body fat, lean mass, abdominal, waist and biceps circumference, abdominal skinfold thickness, tricipital skinfold thickness, dynamometry, sit to stand 5 repetitions test, perceived quality of life, acquired knowledge, self-efficacy, and usability.

For participants with T1D, hypoglycemic events (number of episodes of at least 15-minute duration with a glucose concentration of <70 mg/dL according to the CGM and manually registered episodes), HbA_1c_, average glucose (average glucose in mg/dL over the last 14 days), glucose management indicator (a measure of glycemic control calculated from average glucose, which is an estimation of HbA_1c_) and time in target range (% of time in the last 14 days that glucose is within (70-180mg/dL), below (<70 mg/dL), above (181-240 mg/dL), or significantly above (>240 mg/dL) the recommended target will be measured.

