#### Biomedical Outcomes

A blood test and physical examination were only carried out in Spain. A blood test was performed at the beginning and end of the study to measure blood count, creatinine, urea, glucose, glutamic pyruvic transaminase, glutamic oxaloacetic transaminase, gamma-glutamyl transferase, total cholesterol, HDL cholesterol, and triglycerides in all participants. Automated, routine colorimetric methods are used. Non-HDL cholesterol is calculated by subtracting HDL from total cholesterol, and low-density lipoprotein cholesterol is estimated using Friedewald’s formula [39]. HbA_1c_ was measured by High-Performance Liquid Chromatography (using Diabetes Control and Complications Trial standards, following National Glycohaemoglobin Standardisation Programme) in people with T1D only.

As part of the physical examination, the patient’s weight and height were measured to calculate BMI. Measurements of the abdomen, arm, and calf circumference are taken with a non-extensible measuring tape. Grip strength is assessed using a Jamar dynamometer, and a Holtain plicometer (Holtain Ltd) is used to measure the triceps skinfold. Body fat and muscle mass are estimated using a Tanita DC-360 (Tanita) bioimpedance meter. Arm muscle circumference is calculated from the triceps skinfold and arm circumference measurement. Muscle quality is calculated based on the muscle mass from the bioimpedance analysis and the grip strength measurement [40]. Finally, the functional test sit-to-stand with 5 repetitions is performed [41].

For participants with T1D, time in relevant ranges (see above), average glucose, glucose management indicator, and hypoglycemic events are recorded by the app from a CGM FSL 2 or 3 (Abbott). Hypoglycemic events are also recorded or confirmed manually.

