### Power and Sample Size

The sample size was calculated for the primary outcome (Likert scale from 1 to 10 with a target defined by the participant). A population of people with T1D was used as the reference population, based on a previous study [38,49]. The common SD in the intervention and control groups is assumed to be 2.07 [38]. With a significance level of 0.05 and a power of 0.8 in a 2-sided 2-sample *t* test (2-tailed), 47 subjects are necessary in both groups to detect a statistically significant difference greater than or equal to 1.3 units. Allowing for a potential loss to follow-up of 10%, we estimated a total required sample size of 52 participants in each group. Participants with T1D are only recruited in Spain. All 3 centers aimed to recruit an equal number of participants, that is, 36 participants each (aiming at a total of 108).

The analyses will primarily be performed on the total sample for common outcomes. Regarding the group of participants with T1D, as the study lacks the power to detect clinically relevant changes in T1D-specific clinical outcomes, no definitive conclusions will be drawn from these results. Instead, the results will inform sample size estimation and the design of a subsequent trial targeting the T1D population specifically.

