## Results

The clinical trial began in January 2025. A total of 88 participants were recruited from 3 centers: 34 from Spain, 34 from Norway, and 20 from Romania (Figure 3). Participants were randomized at a ratio of 1:1 to either the intervention or control group (42 participants in the intervention group and 46 in the control group). Each participant was observed for up to 12 weeks in total, with the follow-up period ending in June 2025. The data are currently being analyzed and are expected to be published in 2026.

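### The total-sample sentence and the bar on firm conclusions do not fit the 16 clinic-measured secondary outcomes, which come from Spain only (at most 34 of 88 participants)

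*Protocol article*

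**What the plan says.** All references are to the protocol article.

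- **Power and Sample Size**, on the analysis population: "The analyses will primarily be performed on the total sample for common outcomes".
- **Power and Sample Size**, on interpretation: "as the study lacks the power to detect clinically relevant changes in T1D-specific clinical outcomes, no definitive conclusions will be drawn from these results". The same section says that T1D participants are recruited only in Spain.
- **Outcomes, Overview** gives one list of secondary outcomes with no restriction by center, then a separate paragraph for T1D participants. The first list runs from app use and behavior ("frequency of app use, time spent using the app, consistency in data recording, changes in eating habits, increase in physical activity") through blood and body measures ("low-density lipoprotein cholesterol, non-HDL cholesterol, triglycerides, weight, BMI, body fat, lean mass") to anthropometry and function ("abdominal, waist and biceps circumference, abdominal skinfold thickness, tricipital skinfold thickness, dynamometry, sit to stand 5 repetitions test"), and ends with questionnaire outcomes.
- **Biomedical Outcomes**: "A blood test and physical examination were only carried out in Spain". The Intervention section and footnote b of Table 1 agree.
- **Statistical Analysis** plans an intention-to-treat analysis of everyone randomized and a .05 significance threshold with no distinction by outcome. The primary comparison is also to be adjusted for center, and change outcomes for their baseline value. T1D status is in neither model, although Randomization and Blinding names it as a stratification factor beside center.
- **Results** gives recruitment as "34 from Spain, 34 from Norway, and 20 from Romania", with 42 participants in the intervention arm and 46 in the control arm.
- **Anticipated Findings** (Discussion) acknowledges that the biomedical data come from one center and that the sample may be too small for many secondary outcomes, T1D above all.

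**The concern.** The methods text gives one analysis population for the common outcomes, and more than half of the common secondary outcomes cannot be analyzed in it. No alternative population is named for them.

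The interpretation rule is also uneven. Low power is the stated reason for withholding firm conclusions on T1D-specific outcomes. The lipid, body composition and function outcomes come from the single center that supplies every T1D participant, so they too rest on a small part of the sample, yet the rule does not reach them.

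At stake is how a lipid or body composition result will be read. With no rule in the methods, a P value below .05, or a null result, could be taken as a finding of a three-country trial of 88. It would rest on one center and at most 34 people, a mix of T1D and general-population participants.

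**Working it through.** **1. Count of outcomes (Outcomes, Overview).**
- App use and behavior: frequency, time, consistency, eating, physical activity, smoking, alcohol, sun protection = 8 (smoking and alcohol counted separately).
- Blood: total, HDL, LDL and non-HDL cholesterol, triglycerides = 5.
- Body and function: weight, BMI, body fat, lean mass, three circumferences, two skinfolds, dynamometry, sit-to-stand = 11.
- Questionnaires: quality of life, knowledge, self-efficacy, usability = 4.

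The total is 8 + 5 + 11 + 4 = 28, of which 5 + 11 = 16 come from the blood test and physical examination. The app questionnaires also ask for weight and height (Intervention, lifestyle assessment) and were completed at all centers. If those self-reports were used, weight and BMI could exist outside Spain, leaving 16 − 2 = 14.

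**2. Share of the sample.** 34 + 34 + 20 = 88, and 34/88 = 38.6%, before any loss to follow-up.

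**3. The plan's own power figure.** The only one is for the primary outcome: SD 2.07, difference 1.3, two-sided 0.05, power 0.80, 47 per group. The normal formula n = 2(1.960 + 0.842)² × (2.07/1.3)² gives 40, and the exact t test gives 41. So 47 is not reproduced, but it errs on the cautious side and nothing below uses it. The plan gives no power figure for the biomedical outcomes.

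**4. Detectable effect, unadjusted.** The normal approximation is d = (1.960 + 0.842) × √(1/n₁ + 1/n₂). The exact column solves the noncentral t for 80% power.

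| Set | n₁ / n₂ | Normal | Exact t |
|---|---|---|---|
| All randomized | 42 / 46 | 2.802 × 0.2134 = 0.60 | 0.60 SD |
| Spain, even split (assumed) | 17 / 17 | 2.802 × 0.3430 = 0.96 | 0.99 SD |
| Spain, uneven split (assumed) | 14 / 20 | – | 1.01 SD |
| Spain after about 10% loss (assumed) | 15 / 15 | – | 1.06 SD |
| Spain at the planned 36 | 18 / 18 | – | 0.96 SD |

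The even split is an assumption. It follows from 1:1 allocation stratified by center, but the article does not report the split within Spain. The result barely depends on it. The last row shows that the limit comes from the design, not from the recruitment shortfall.

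**5. Detectable effect with baseline adjustment.** Multiply by √(1 − r²), where r is the baseline-to-end correlation. The article gives no value, so a range is shown.

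| Assumed r | √(1 − r²) | Spain 17/17 |
|---|---|---|
| 0.5 | 0.866 | 0.86 SD |
| 0.7 | 0.714 | 0.71 SD |
| 0.8 | 0.600 | 0.59 SD |
| 0.9 | 0.436 | 0.43 SD |

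The same factor applies to the full sample: 0.605 × 0.866 = 0.52 SD at r = 0.5 and 0.605 × 0.436 = 0.26 SD at r = 0.9. At any given r, restriction to Spain raises the detectable effect by a factor of 0.991/0.605 = 1.64.

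**6. Stratification.** Within Spain, center is constant. T1D status is then the only stratification factor left, and the planned models for change outcomes do not include it.

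**The case against.** The strongest reply is that there is no contradiction. The sentence on common outcomes stands next to the one on T1D-specific outcomes, so common can mean common to both populations, and total sample can mean that T1D and general-population participants are pooled. The sentence also says primarily. The article states several times that the examinations took place only in Spain, and its discussion concedes both the single-center data and a size that may not suffice for many secondary outcomes. Naming an analysis set for each secondary outcome is usual SAP content, and that document is not shown. The trial was sized for the primary outcome only, so low power on a secondary outcome is not in itself an error. Because allocation was stratified by center, a comparison within Spain is still a randomized one.

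Most of this stands. It makes the population sentence imprecise rather than flatly contradictory, and failure to name the Spanish subset would not by itself be a finding. What it leaves unanswered is the interpretation rule. The article chose to state in its methods which outcomes are too weakly powered for firm conclusions, and drew that line around T1D-specific outcomes alone. The discussion's caution is wider than the rule, and the two should agree.

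A reader might go further and infer that the trial intends to claim effects on lipids or body composition from about 17 people per arm. The documents do not support that. No such claim is planned, and the absence of a bar is not a plan to conclude. Nor can it be said how close the power for these outcomes is to that for the T1D outcomes, because the number of T1D participants enrolled is not given.

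**Conclusion.** The point holds as a minor one. For the 16 clinic-measured common outcomes (14 if self-reported weight and BMI are used elsewhere), neither the total-sample analysis nor an analysis of everyone randomized can be carried out, since at most 34 of 88 participants have data. The methods restriction on conclusions does not cover these outcomes, although the discussion accepts the reason for it.

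An unadjusted comparison in Spain can detect only about 1 SD with 80% power, against about 0.60 SD on all 88. Baseline adjustment, which is already planned, improves this to between 0.86 and 0.43 SD. These figures assume about 17 per arm and correlations of 0.5 to 0.9, none of which the article states.

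The primary outcome is unaffected. It should not be inferred that the other 28 − 16 = 12 secondary outcomes are fully available in both arms. Behavior Change measures diet, tobacco, alcohol and sunscreen use from diary entries, while Control Group says the control version has no diary but that data are collected similarly. The article leaves that unresolved.

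**What to change.** - **Power and Sample Size:** state that the clinic-measured outcomes are analyzed in the Spanish participants. Extend the existing sentence that "no definitive conclusions will be drawn from these results" to these outcomes, in line with the limitation already given in the discussion. Report them as estimates with 95% CI and the number analyzed per arm.
- **Statistical Analysis:** add T1D status, a stratification factor, to the baseline-adjusted models for these outcomes.
- Do not describe the remaining 12 outcomes as available for everyone in both arms until the source of the diary-based outcomes in the control arm is clear.

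This needs no new data: it is a change of wording and one covariate. The cost is that the stated reach of the biomedical results becomes less favorable. Because the article describes the data as still being analyzed, the change should be dated and made before the allocation is revealed to the analysts, whom the article describes as blinded.

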### Ethical Considerations

It was submitted to and approved by the Las Palmas Ethics Committee in September 2024 (reference 2024-330-1). It was submitted to clinicaltrials.gov in June 2024 and approved with ID NCT06918444. An insurance policy was signed for the entire duration of the study, which was conducted during the first half of 2025.

Potentially eligible participants were given an informed consent form and an information sheet about the study, in the relevant language (Spanish, Norwegian, Romanian, or English). Those who agreed to participate and signed the form were enrolled in the study. Participants could withdraw from the study at any time. The study participants’ data were anonymized during the study. Participants were not paid for entering or remaining in the study.

The WARIFA project places strong emphasis on data protection, algorithmic support, user autonomy, and transparency in AI‑driven recommendations. Personal and health‑related data are processed under explicit informed consent in accordance with General Data Protection Regulation, with safeguards such as pseudonymization, encryption, strict access control, and privacy‑by‑design measures embedded throughout the system architecture. AI algorithms operate on validated, pseudonymized datasets within a secure environment, providing personalized risk assessments and lifestyle recommendations without engaging in diagnostic or therapeutic decision‑making, ensuring that users remain in control of their health choices and can withdraw consent or correct their data at any time. Transparency is supported through clear privacy policies, detailed consent procedures, and user‑facing explanations of data flows, processing purposes, and the nonclinical nature of the AI outputs, thereby promoting informed engagement and preserving user autonomy while maintaining high ethical and regulatory compliance standards.

## Results

The clinical trial began in January 2025. A total of 88 participants were recruited from 3 centers: 34 from Spain, 34 from Norway, and 20 from Romania (Figure 3). Participants were randomized at a ratio of 1:1 to either the intervention or control group (42 participants in the intervention group and 46 in the control group). Each participant was observed for up to 12 weeks in total, with the follow-up period ending in June 2025. The data are currently being analyzed and are expected to be published in 2026.

**Figure 3 figure3:**
[figure not shown]
Flowchart of participant recruitment.

## Discussion

### Anticipated Findings

The RCT we describe aims to assess the short-term effectiveness of the WARIFA app in promoting users’ healthy behaviors and self-management of T1D. Our hypothesis is that dynamic, personalized recommendations can achieve self-defined objectives and healthy behavior changes to a larger extent than general recommendations for all users.

Other mHealth apps have been used for behavior change and disease management in patients with hypertension and obesity [50,51], although they do not provide estimates of the risk of NCDs.

The main strengths of this trial are that it is conducted in 3 European countries and includes a fairly large and heterogeneous sample size, which should support the applicability of the results. Furthermore, the use of a low-intervention app and a physical activity monitor as control, as well as the double-blind nature of the trial, reduces the risk of bias. The WARIFA app can provide personalized risk estimations for the major NCDs over the next 10 years, as well as identifying the habits to change and the most effective way to do so for each individual. This is in contrast to the generic messages typically used in community-based prevention. The app is able to deliver these personalized messages to participants’ devices to encourage adherence. A key strength of the WARIFA project is its rigorous commitment to data protection, robust algorithmic support, user autonomy, and full transparency in AI‑driven recommendations.

We also acknowledge some limitations in the design of the trial. Although we believe that the number of participants is appropriate for an initial evaluation of the WARIFA app, it may not be sufficient to assess many of the secondary outcomes addressed, especially in T1D. Another limitation is that the biomedical outcomes (anthropometry and blood tests) are performed at one of the centers only, and these data will not be available for all participants. Restrictions also include the fact that the WARIFA app is only compatible with Android mobile phones, as well as certain activity devices and glucose sensors. mHealth apps have boomed in recent years as a tool that is free, voluntary, and easy to obtain. However, many users uninstall the app shortly after installation [52].

Many mHealth apps have demonstrated their effectiveness in promoting healthy habits and managing chronic diseases such as diabetes and cardiovascular conditions; most of them rely on short-term interventions and have limitations in terms of long-term applicability and accessibility for the entire population [53-56]. In contrast, the WARIFA app has been designed using an integrative, personalized approach that targets adults of all ages, including those with low digital literacy skills and seldom heard populations [57,58], areas that are often missed by similar apps. However, long-term applicability is not assessed.

Furthermore, the WARIFA app was developed by actively incorporating feedback from potential users and health care professionals through focus groups. This participatory process allowed the design, functionality, and content to be tailored to users’ real needs. This participatory process improves usability, acceptability, and scalability. WARIFA aims to promote healthy behaviors through a more inclusive and user-centered tool than many existing apps.

### Conclusions

This randomized, double blind, controlled, parallel-group trial assesses the short-term effectiveness of the WARIFA health app in promoting healthy behaviors. It will also allow us to identify its weaknesses and limitations, to further improve and develop this, or similar apps. A longer-term study would be needed to assess its long-term effects, including those on the risk for major NCDs, as well as its integration into health care systems.

## Abbreviations

AI: artificial intelligence
CGM: continuous glucose monitoring
COPD: chronic obstructive pulmonary disease
CVD: cardiovascular disease
EU: European Union
FSL: Free Style Libre
HbA1c: glycosylated hemoglobin A1c
HDL: high-density lipoprotein
MAUQ: mHealth App Usability Questionnaire
mHealth: mobile health
NCD: noncommunicable disease
RCT: randomized controlled trial
SDSCA: Summary of Diabetes Self-Care Activities
SPIRIT: Standard Protocol Items: Recommendations for Intervention Trials
SPIRIT-AI: Standard Protocol Items: Recommendations for Intervention Trials–Artificial Intelligence
SUS: System Usability Scale
T1D: type 1 diabetes
T2D: type 2 diabetes
ViDa1: Life with Type 1 Diabetes (Vida con Diabetes tipo 1)
WARIFA: Watching the Risk Factors
